# Evaluating the safety, effectiveness and acceptability of treatment of incomplete second-trimester abortion using misoprostol provided by midwives compared with physicians: study protocol for a randomized controlled equivalence trial

**DOI:** 10.1186/s13063-019-3490-5

**Published:** 2019-06-21

**Keywords:** Post abortion care, Misoprostol, Second trimester, Task sharing, Incomplete abortion, Contraception, Uganda

## Abstract

**Background:**

A large proportion of abortion-related mortality and morbidity occurs in the second trimester of pregnancy. The Uganda Ministry of Health policy restricts management of second-trimester incomplete abortion to physicians who are few and unequally distributed, with most practicing in urban regions. Unsafe and outdated methods like sharp curettage are frequently used. Medical management of second-trimester post-abortion care by midwives offers an advantage given the difficulty in providing surgical management in low-income settings and current health worker shortages. The study aims to assess the safety, effectiveness and acceptability of treatment of incomplete second-trimester abortion using misoprostol provided by midwives compared with physicians.

**Methods:**

A randomized controlled equivalence trial implemented at eight hospitals and health centers in Central Uganda will include 1192 eligible women with incomplete abortion of uterine size > 12 weeks up to 18 weeks. Each participant will be randomly assigned to undergo a clinical assessment and treatment by either a midwife (intervention arm) or a physician (control arm). Enrolled participants will receive 400 μg misoprostol administered sublingually every 3 h up to five doses within 24 h at the health facility until a complete abortion is confirmed. Women who do not achieve complete abortion within 24 h will undergo surgical uterine evacuation. Pre discharge, participants will receive contraceptive counseling and information on what to expect in terms of side effects and signs of complications, with follow-up 14 days later to assess secondary outcomes. Analyses will be by intention to treat. Background characteristics and outcomes will be presented using descriptive statistics. Differences between groups will be analyzed using risk difference (95% confidence interval) and equivalence established if this lies between the predefined range of − 5% and + 5%. Chi-square tests will be used for comparison of outcome and *t* tests used to compare mean values. *P* ≤ 0.05 will be considered statistically significant.

**Discussion:**

Our study will provide evidence to inform national and international policies, standard care guidelines and training program curricula on treatment of second-trimester incomplete abortion for improved access.

**Trial registration:**

ClinicalTrials.gov, NCT03622073. Registered on 9 August 2018.

**Electronic supplementary material:**

The online version of this article (10.1186/s13063-019-3490-5) contains supplementary material, which is available to authorized users.

## Background

Globally, 303,000 maternal deaths occurred in 2015 [1], with 11% of maternal deaths and a large number of morbidities attributable to consequences of unsafe abortion [2–4]. More than 97% of unsafe abortions occur in sub-Saharan Africa, with the rates of unplanned pregnancy ending in an abortion increasing in low-income settings while decreasing in high-income countries [4]. Reasons behind the high unsafe abortion rates in low-income settings are restrictive abortion laws, high unmet need for contraception and low women’s status [3, 5].

Post-abortion care (PAC), defined as the comprehensive treatment of women presenting after spontaneous or induced, safe or unsafe abortion, is an effective intervention to decrease maternal mortality globally [6]. PAC comprises five key elements: emergency treatment, family planning, counseling, other reproductive and related health services, and community–service provider partnerships [7]. Evidence shows that PAC services can be safely offered by midwives in the first trimester [8, 9]. Evidence is lacking on whether PAC can also be safely offered by midwives in the second trimester particularly in rural settings of low-income countries where physicians are scarce, such as Uganda.

Uganda has a high total fertility rate (5.4 children per woman), a low contraceptive prevalence rate of 39% and an unmet need for contraception of 28% [10]. More than half of all pregancies are unintended due to insufficient knowledge of and misinformation about contraception, inaccessibility to family planing services and ineffective contraceptive use [11]. Multiple obstacles to contraceptive use, such as misconceptions and fears related to contraception, gender–power relations, sociocultural factors and health care service barriers have been cited [12, 13]. Induced abortion in Uganda is restricted and legally permitted only to save a woman’s life [14]. As a result, women often resort to unsafe abortion “that’s either performed by a person lacking the necessary skills or in an environment that does not conform to minimal medical standards” [6]. Of the estimated 314,304 women who undergo unsafe abortions each year, about 128,682 experience complications with only 85,000 obtaining care [15]. Consequently, it is estimated that complications from spontaneous and unsafe abortions contribute to 8% of maternal mortality in Uganda [16]. Post-abortion complications are exacerbated by lack of resources, delayed care-seeking and harmful abortion practices [17]. In some instances, women will fear accessing care due to stigma that is intrinsic, or from family members, community providers and even health providers [18]. Although abortion in Uganda is restricted, treatment of post-abortion complications is a critical component of emergency obstetric care services offered throughout the spectrum of health facilities from Health Centre IIs to hospitals [19, 20]. A study in 2014 cited midwives as the main implementers of PAC in the first trimester, often only consulting a physician when a complication arises [21].

Low-income countries like Uganda suffer from shortages and an unequal distribution of trained health care providers. Almost two thirds of all physicians work in the urban regions, which serve less than one third of the population [20]. While the Ministry of Health (MOH) policy in Uganda allows both physicians and midwives to treat women with first-trimester incomplete abortions, it restricts management of second-trimester incomplete abortion to physicians [19]. The standard treatment for bleeding following an abortion in the first trimester is either misoprostol or manual vacuum aspiration, while sharp curretage by a doctor is done for women in the second trimester. The need for a surgical intervention in a setting where there is a scarcity of trained providers, sterile equipment and poor access to high-level centers limits women’s access to safe PAC, especially in remote areas. Observations in clinical practice show that the number of incomplete abortions in the second trimester are at least as high as in the first trimester in Uganda.

Evidence is compelling that the prostaglandin E1 analogue misoprostol is effective medication for first-trimester incomplete abortions [8, 22], and that there is no difference whether provided by physicians or midwives [8, 23, 24]. The choice of an equivalence trial design is to provide evidence that use of misoprostol for PAC in the second trimester when administered by physicians or midwives is equally safe, effective and acceptable. In view of the severe shortage of medical staff in rural areas and importance of task sharing to improve productivity and efficiency within a health system [21, 25, 26], the overall aim of the study is to compare the safety, effectiveness and acceptability outcomes of treatment for incomplete abortion using misoprostol when provided by midwives versus physicians in Uganda.

## Methods

### Trial design

The study uses a multicenter randomized controlled equivalence design to compare the management of second-trimester abortion complications with misoprostol to be provided by a midwife or a doctor in a ratio of 1:1 (Fig. 1). The trial follows recommendations of the modified Consort guidelines for equivalence trials [27] and the Helsinki Declaration [28]. A populated Standard Protocol Items: Recommendations for Interventional Trials (SPIRIT) checklist is provided in Additional file 1.

**Fig. 1 Fig1:**
[figure not shown]
Trial design. ITT intention to treat

### Study setting

The study is implemented in the central region of Uganda, which has a higher estimated induced abortion rate compared to the national average (52 versus 39 per 1000 live deliveries) and an accompanying huge caseload of women treated for abortion complications [29]. All selected study sites are public health facilities, equipped to provide comprehensive emergency obstetric services in rural, peri-urban and urban areas. They comprise Health Centre IVs (the lowest health care level staffed with both physicians and midwives), district hospitals and a regional referral hospital, all located within 1–2 h from Kampala, the capital city of Uganda.

Health facilities identified for inclusion in the trial have an average caseload of about 90 women with incomplete second-trimester abortions per month and sufficient staff to establish a group of 138 midwives plus other nurse-midwifery cadres at certificate, diploma and degree level and 37 physicians based on mapping of facility records data for January–June 2017, done by one of the researchers [name]. Hospital-based study sites have an average (median) of 5 (6) physicians and 19 (20) midwives, whereas the Health Centre IV study sites have an average (median) of 3 (3) physicians and 13 (16) midwives. We assume that these staff will provide an adequate pool of health providers to conduct the study. The cadre of physicians consist of medical officers and obstetricians/gynecologists with 5 years of medical training and an additional 3 years postgraduate training, respectively. Nursing and midwifery preservice programs in Uganda offer certificate, diploma or degree qualifications after 18 months, 3 years and 4 years of training, respectively. Competences are most often in midwifery and nursing, and there is provision for upgrading to a higher qualification with additional training. In this trial, a midwife is defined as a health provider who has obtained midwifery training competence as part of their preservice or additional training program.

### Eligibility criteria

Women with abortion complications presenting with vaginal bleeding, uterine contractions, uterine size more than 12 weeks but no more than 18 weeks by palpation, history of partial expulsion and an open cervical os will be included in the study. We will exclude women with known age younger than 15 years, allergy to misoprostol, unstable hemodynamic status (systolic blood pressure < 90 mmHg) and shock, signs of pelvic infection and/or sepsis, previous caesarean delivery/uterine scar, suspected extra-uterine pregnancy, perforation of the uterus, injury to the surrounding organs, heavy vaginal bleeding, severe abdominal pain, cervical tear, uterine size ≤12 or > 18 weeks, temperature greater than 38 °C and current molar abortion.

### Recruitment

The study aims to recruit 50 eligible patients monthly over a 24-month period. The health facility staff in all potential recruitment areas, including maternity wards, female wards, emergency wards and outpatient clinics, will be sensitized about the study and encouraged to alert the study team members when a probable case is identified. Notices/posters indicating brief study details and contact persons will be placed at potential recruitment sites of the facility as reminders to staff. All participants are given a modest transport reimbursement of UGX 10,000 (USD 3) for follow-up visits.

### Interventions

#### Enrollment

All women presenting with signs of an incomplete abortion are screened for eligibility by a trained midwife using a predefined checklist. The research assistant obtains written informed consent through a process that involves: giving the participant information concerning the study; providing adequate opportunity for the participant to consider all options; responding to the participant’s questions; ensuring that the participant comprehends this information; obtaining the participant’s voluntary agreement to participate; and continuing to provide information as the participant or situation requires. Women excluded at this point are registered and the reason for exclusion indicated.

#### Procedure

All assessment and care are provided in a way that ensures privacy and confidentiality. Eligible women who consent undergo a clinical assessment by either a midwife (intervention arm) or a physician (control arm). The clinical assessment includes: history taking (sociodemographic information, last menstrual period (LMP), assessment for chronic medical conditions, obstetric and gynecological history, previous use of contraception and details of presenting symptoms); general physical examination and vital signs (pulse, blood pressure and temperature); and abdominal examination to assess the size of the uterus and a vaginal examination to assess cervical opening, bleeding and signs of genital infections.

The World Health Organization (WHO), in their 2012 safe abortion technical and policy guidance, recommend that the misoprostol regimen for second-trimester termination of pregnancy [6] can be used for incomplete abortion management: 400 μg misoprostol sublingual every 3 h up to five doses. Each treatment dose consists of two 200 μg tablets of misoprostol administered sublingually by the allocated health care provider and this is repeated every 3 h for a maximum of five doses or until a complete abortion is confirmed. The allocated health provider to whom a woman is randomized assesses for presence of side effects, vaginal bleeding and uterine contractions, measures blood pressure and pulse and also records any medication given at 3-h intervals before the next dose of misoprostol is given. The participant completes the full course of treatment under direct observation while at the health facility to ensure adherence. When the participant reports an expulsion, a health provider in the allocated arm performs a clinical assessment to diagnose a complete abortion and records the time of completion, and an independent assessor verifies that the main outcome has been achieved. The expelled products of conception are examined to ascertain the type, whether placental tissue only or whole fetus and placental tissue. All women receive oral nonsteroidal anti-inflammatory drugs starting when the first dose of misoprostol is administered and prophylactic oral antibiotics – amoxicillin 500 mg and metronidazole 400 mg every 8 h for 5 days [30].

In the case that no complete abortion has been achieved within 24 h from the time the first dose of misoprostol was administered, a doctor performs a surgical method of uterine evacuation using MVA or blunt curettage. Patients can also be discontinued from medical management and surgical management instituted if their condition worsens during treatment or on request. All participants are discharged 4 h after completing the abortion if there are no complications. Before discharge, women receive detailed information regarding abnormal symptoms (fever, foul smelling vaginal discharge, bleeding and pain), when to seek care, and contraceptive counselling and provision, and advised to return for a follow-up visit 14 days after treatment. A detailed description of the study participant timeline is provided in Fig. 2.

**Fig. 2 Fig2:**
[figure not shown]
Standard Protocol Items: Recommendations for Interventional Trials figure—participant enrolment and follow-up. PAC post-abortion care

### Outcomes

The primary outcome is complete abortion requiring no surgical intervention within 24 h of initiating treatment. A 24-h timeframe was chosen for clinical relevance given that the participants will be monitored at the health facility. Clinical assessment for the primary outcome includes physical and pelvic examination with attainment of a complete abortion based on cessation of uterine cramps and vaginal bleeding and a closed cervical os. An ultrasound scan is not used to diagnose a complete abortion, given its low predicting value to indicate the need of additional surgical intervention. Ultrasound scan measurement of endometrial thickness as an indicator of a complete abortion actually biases toward increased surgical interventions without significantly improving patient outcomes [31].

Secondary outcomes are assessed at the 2-week follow-up visit and include: excessive vaginal bleeding, defined as soaking more than three pads in an hour; abdominal pain, defined as discomfort experienced in the lower abdomen and intensity measured using a visual analogue scale with a minimum score of 0 representing no pain and a maximum score of 10 representing most pain; unscheduled visits, defined as participants presenting at the study site when not expected, need for additional medical treatment and experience of misoprostol side effects; sepsis, defined as presence of fever with temperature greater than 38 °C, pus or offensive vaginal discharge; time from induction (first dose of misoprostol) to completion and total dose of misoprostol given; women’s acceptability of the PAC provider with acceptability defined as positive reporting of treatment experience, recommendation of method to a friend or reuse of same method; and contraceptive uptake and discontinuation over a period of 1 year.

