### Data collection methods

The information on history, enrolment, procedures and outcomes is collected using an interviewer-administered pretested structured questionnaire and structured clinical notes. All health workers undertake a standardized 2-day training in misoprostol use for management of incomplete abortion and study procedures. Key areas in the training content include: making a diagnosis of incomplete abortion, use of misoprostol for uterine evacuation, pain relief, post-abortion counseling and values clarification, contraceptive counselling and provision, study procedures, adverse event reporting, danger signs and management of complications. Evaluation of training is done using pre and post knowledge assessments. All research assistants also receive training on research conduct prior to the study. Key areas covered include: research ethical principles, informed consent process, data collection and storage procedures and strategies for retention of study participants. All investigators are trained in good clinical practice. The strategies implemented to promote retention in the study include: clearly informing participants of the study procedure and follow-up schedule, assessing the main outcome before discharge, giving specific follow-up review dates and obtaining at least two phone contacts to ensure communication for follow-up. We conduct continuous process evaluation to ascertain reasons for loss to follow-up, identify and implement context-specific mitigating actions and, in addition, record and analyze reasons for nonadherence or nonretention in the study.

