### Harms

Categories of serious adverse events (SAEs) in this study include death, disability/incapacity, life-threatening sepsis, hospitalization longer than 48 h and blood transfusion for severe hemorrhage. A SAE will be considered unexpected if it is not described in the protocol. SAEs will be recorded as study related only if the participant has signed the consent form and started the intervention. These events will be recorded throughout the time the participant is admitted to the health facility. SAEs occurring after the participant has completed the first follow-up visit will not be reported unless the principal investigator feels that the event may have been caused by the protocol procedure. The PI will promptly inform the institutional review board if a SAE occurs. In the case of physical injury resulting from participation in the study, participants will receive medical treatment at a public health facility until resolution or stabilization.

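### Unscheduled visits count only at the study site, and the serious-event rules omit short readmissions and leave discharge to day 14 unclear, so two post-discharge safety measures can miss events

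*Protocol article*

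**What the plan says.** **Unscheduled visits.** The Outcomes section lists, as a secondary outcome, "unscheduled visits, defined as participants presenting at the study site when not expected". The same item continues with "need for additional medical treatment and experience of misoprostol side effects". The punctuation does not show whether these are separate outcomes or part of the visit definition.

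**Other post-discharge outcomes.** "Secondary outcomes are assessed at the 2-week follow-up visit". Two of them are defined by symptoms or signs, with no condition on where care was sought: "excessive vaginal bleeding, defined as soaking more than three pads in an hour" and "sepsis, defined as presence of fever with temperature greater than 38 °C, pus or offensive vaginal discharge". Abdominal pain is scored on a visual analogue scale. Under Data collection methods, the information is "collected using an interviewer-administered pretested structured questionnaire and structured clinical notes".

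**Serious adverse events.** The Harms section names death and disability or incapacity, followed by "life-threatening sepsis, hospitalization longer than 48 h and blood transfusion for severe hemorrhage". It says events are recorded while the woman is admitted to the health facility. It then says events after the first follow-up visit are not reported unless the principal investigator suspects a protocol procedure.

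**Setting.** The Background describes treatment of post-abortion complications as part of "emergency obstetric care services offered throughout the spectrum of health facilities from Health Centre IIs to hospitals". The Study setting section says the sites are Health Centre IVs, district hospitals and a regional referral hospital.

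**The concern.** The article gives safety as part of its overall aim, and its Data monitoring section calls safety one of the main issues under study. Women without complications leave 4 h after completion, so most of the time to day 14 is spent away from the site. Two of the measures covering that time have gaps by definition, even if the plan is followed exactly.

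- A woman who goes to a nearer facility with bleeding or fever does not count as an unscheduled visit.
- A woman readmitted for 48 h or less, not transfused and without life-threatening sepsis, death or disability, meets no listed serious-event category. Nor does a life-threatening event of another cause, unless it leads to one of the listed outcomes.

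The 48 h threshold makes sense for a prolonged index stay, which already includes up to 24 h of treatment. The article does not say whether it is also meant for readmissions.

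At stake is how the between-arm comparison of these two measures is read. If many events are missed, a non-significant result may be taken as evidence of equal safety when it partly reflects incomplete ascertainment.

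**Working it through.** **1. What each definition captures.** Take a woman with bleeding or fever between discharge and day 14.

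| Event | Unscheduled visit? | Listed serious event? | Symptom outcome at 2 weeks? |
|---|---|---|---|
| Outpatient care at study site | Yes | No | Yes, if definition met |
| Outpatient care elsewhere | No | No | Yes, if definition met and elicited |
| Readmitted to study site, 30 h, no transfusion | Yes | No | Yes, if definition met |
| Readmitted elsewhere, 30 h, no transfusion | No | No | Yes, if definition met and elicited |
| Readmitted elsewhere, longer than 48 h | No | Yes, but unclear whether it is recorded | Yes, if definition met and elicited |

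The fourth row is missed by both measures. The last row shows the window problem. One sentence in Harms ties recording to the time admitted; another implies that events count up to the first follow-up visit. If the admission meant is the index stay, the days from discharge to day 14 are not covered. If it means any admission, it is not clear that one elsewhere is included.

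**2. The plan's own figure.** No figure is given for safety outcomes. The stated sample size supplies the arm size for the illustration, and it reproduces: n = [2 × 0.9 × 0.1 × (1.960 + 0.842)²] / 0.05² = 566 per arm (rounded up), and 1132 / 0.95 = 1192. The present point does not affect this figure.

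**3. Equal under-capture.** Let p₁ and p₂ be the true event risks and c the share captured, the same in both arms. The recorded difference is c·p₁ − c·p₂ = c × (p₁ − p₂). The recorded risk ratio stays at p₁/p₂.

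Neither the risks nor c is in the article. All values below are assumptions. With 566 per arm, SE = √{[c·p₁(1 − c·p₁) + c·p₂(1 − c·p₂)] / 566}. Power is for a two-sided 5% comparison of two proportions.

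For 6% v 3%:

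| Captured | Recorded risks | Difference (95% CI), points | Power |
|---|---|---|---|
| 100% | 6% v 3% | 3.0 (0.6 to 5.4) | 68% |
| 75% | 4.5% v 2.25% | 2.25 (0.15 to 4.35) | 55% |
| 50% | 3% v 1.5% | 1.5 (−0.2 to 3.2) | 40% |

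For 10% v 5%, power falls from 89% to 78% and 60% at the same capture levels. For 4% v 2%, it falls from 51% to 40% and 28%.

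**4. Unequal capture.** Again with true risks of 6% (midwife arm) and 3% (physician arm), a difference of 3.0 points:

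- 50% and 75% captured: 0.06 × 0.50 − 0.03 × 0.75 = 0.75 points
- 75% and 50% captured: 0.06 × 0.75 − 0.03 × 0.50 = 3.0 points
- 90% and 60% captured: 0.06 × 0.90 − 0.03 × 0.60 = 3.6 points

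The direction of the distortion is therefore not fixed.

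**The case against.** A reader might infer that complications count at all only if the woman returns to the study site. The article does not say that. The site condition belongs to one outcome. Bleeding, pain and sepsis are assessed at a scheduled visit partly by interview, so a woman treated elsewhere can still be recorded. A short readmission to the study site is still an unscheduled visit. This part of the objection stands and limits the point to two measures.

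A reader might also infer that missed events push the trial toward declaring equivalence. They do not: the −5% to +5% rule is stated for the primary outcome, which is assessed before discharge. Other outcomes are compared by chi-square, with Fisher's exact test for side effects, and no margin is stated for them.

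Diversion to other facilities is plausible but not shown. The Background describes where services exist, not where these women go. National policy restricts second-trimester management to physicians, and the sites offer comprehensive emergency obstetric care, so serious cases may well come back. This too stands: the share lost is unknown.

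Finally, an article condenses the full protocol, and its serious-event categories are introduced as what is included, so the full list may be longer. That would excuse an omission. It does not excuse a stated definition that excludes care elsewhere, a stated 48 h threshold, or two stated sentences on recording and reporting that do not fit together.

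**Conclusion.** The point holds for the unscheduled-visit outcome and the serious-event rules, and only for those. As written, the first excludes unplanned care elsewhere. The second excludes readmissions of 48 h or less that meet no other category, limits the life-threatening criterion to sepsis, and leaves discharge to the first follow-up visit unclear.

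The size cannot be derived from the article. Under equal capture, the recorded difference is the captured share of the true one, so 3.0 points becomes 2.25 at 75% and 1.5 at 50%. That rests on assumed risks and an assumed equal share in both arms. A general claim that safety will look more alike than it is would go too far, because unequal capture can shrink the difference, leave it unchanged or enlarge it. The symptom-based outcomes, the primary outcome, its margin and the sample size are not affected.

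**What to change.** - Define an unscheduled visit as any unplanned contact with any health facility or provider for a post-abortion complaint from discharge to day 14. Ask about it at the day-14 interview, or through the phone contacts already collected for women who do not attend. Keep study-site visits as a sub-category, so that women already followed under the current definition remain comparable.
- In the serious-event rules, record every abortion-related readmission whatever its length and every life-threatening event whatever its cause. The 48 h threshold can stay for the index stay.
- Reconcile the two sentences in Harms by stating one recording window that includes discharge to the first follow-up visit.

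The cost is revised wording and a question at an interview that already takes place. The downside is that some self-reported visits will have no records to confirm them, and there will be a few more serious-event reports. Since recruitment began in August 2018, the change would be an amendment with a stated start date.
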